##### Exclusion criteria

Patients with neurological symptom related to UIA, such as sentinel headache, oculomotor paralysis and so on.Patients with additional active intracranial disease including vasculopathy, arteriovenous malformation/fistula, cancer, traumatic brain injury etc.Patients with fusiform, dissecting, blister, traumatic, mycotic/bacterial, myxomatous, and tumor-associated UIAs are excluded.Patients with history of polycystic kidney disease, rheumatic disease or autoimmune disease.Patients with family history of intracranial aneurysm (defined when two direct relatives of patients within three generations have intracranial aneurysms or aneurysmal subarachnoid hemorrhage).Patients with known secondary cause of hypertension.Patients with myocardial infarction, ischemic stroke, symptomatic heart failure during the past 3 months.Patients with a medical condition likely to limit survival to less than 2 years.Patients during pregnancy and perinatal period.Any concurrent serious illness that would interfere with the outcome assessments including hepatic, renal, gastroenterological, respiratory, cardiovascular, endocrinologic, immunologic, and hematologic disease.Inability or unwillingness of patient or legal representative to give written informed consent.Participation in a concurrent interventional medical investigation or clinical trial.

UIA patients who meet the inclusion criteria but do not meet the exclusion criteria will be considered in subsequent randomization.

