### Outcomes and relative definitions

The primary efficacy outcome is UIA instability, including aneurysm growth, rupture or aneurysm-related symptoms during 24-month follow-up. The definitions of UIA instability are listed as follows:

Aneurysm growth is defined as one or more of the following: (1) growth of more than 1 mm in at least one direction, (2) growth of more than 0.5 mm in at least two directions, (3) growth of more than 20% of baseline aneurysm size in any direction, or (4) new appearance of irregularity on the UIA.Aneurysm rupture is diagnosed when patients have the symptoms of non-traumatic subarachnoid hemorrhage (e.g., severe headache and sudden coma) attributable to the target UIA, imaging evidence of hemorrhage on CT or MRI, and/or bloody cerebrospinal fluid from lumbar puncture.Occurrence of aneurysm-related symptoms is diagnosed as sentinel headache (a sudden and severe headache attributable to the UIA within 2 weeks of onset, and without prior history of significant headache within the previous 5 years), oculomotor nerve palsy (a sudden headache with one or several symptoms of pupillary light reflex disappearing, ptosis, or extraocular myoparalysis, ipsilateral to a UIA in the vicinity of the affected oculomotor nerve and without systemic cause such as diabetes), other cranial neuropathy (such as visual field defect secondary to UIA compression of the optic apparatus without alternative cause), or seizure related to UIA inflammation (defined as EEG or clinically determined seizure activity generated from inflammatory changes in the brain parenchyma surrounding the UIA on imaging, and without prior history of seizure or other cause of seizure).

Two investigators who are unaware of the patient’s information assess the occurrence of UIA instability and ischemic brain or cardiac events at 6 months (± 1 month), 12 (± 1 month) months, and 24 (± 1 month) months through monthly follow-up and imaging examinations of UIA.

The primary safety outcome is any ischemic cerebral or cardiac events during 24-month follow-up. This includes one or more of the following: new or more frequent transient ischemic attacks, new clinical or radiological ischemic stroke, angina, new myocardial infarction, or reperfusion therapy for myocardial infarction. Ischemic brain or cardiac events are defined as follows:

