TIA is defined as a transient episode (duration of symptoms < 24 h) of neurological dysfunctions caused by focal brain, spinal cord, or retinal ischemia without showing acute infarction on non-contrasted CT (NCCT).Ischemic stroke is a persistent episode of neurological dysfunctions caused by focal brain, spinal cord, or retinal ischemia, which shows acute hypodense infarction area on NCCT images and T2-weighted MRI.Angina is defined as a transient chest pain or pressure (duration of symptoms < 30 min) caused by insufficient blood flow to the myocardium without significant ST/T changes in ECG and rise of cardiac biomarkers.Myocardial infarction is defined as myocardial necrosis in clinical settings consistent with myocardial ischemia. These conditions can be satisfied by a rise of cardiac biomarkers [preferably cardiac troponin (cTn)] plus at least one of the following: (1) symptoms of cardiovascular ischemia; (2) ECG changes indicative of new ischemia (significant ST/T changes or left bundle branch block); (3) development of pathologic Q waves; (4) imaging evidence of new loss of myocardium or new regional wall motion abnormalities; (5) angiography or autopsy evidence of intracoronary thrombus.

Secondary outcomes are: 1. UIA rupture events during 24-month follow-up; 2. UIA growth events during 24-month follow-up; 3. Change in average Wall Enhancement Index (WEI) at baseline and 24th month. WEI is defined as follows:

Two investigators (with work experience of >10 years, who are blind to the clinical and morphological information) measure the WEI value independently using Vessel-MASS software (Leiden University Medical Center). Three slices with significant enhancement observed by post-contrast VW-MRI at baseline and 24 months will be selected. After tracing the lumen and outer boundaries of the aneurysm wall, the contours of the inner lumen and outer wall of aneurysms will be automatically segmented using the software. If the tracking is not satisfactory, the investigators will manually adjust the contour of the inner cavity and the outer wall. Subsequently, the mean signal intensity (SI) will be calculated automatically using the software. The average and maximum value of the mean SI of the corresponding three slices will be used for further analyses.

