#### Step 3: Outcome evaluation

All patients will be required to complete head CTA at 6 months (± 1 month), 12 (± 1 month) months, and 24 (± 1 month) months during follow-up. VW-MRI examinations are required to be completed at 24 (± 1 month) months after appropriate blood pressure lowering therapy.

Self-record blood pressure and occurrence of any aneurysm-related symptoms or safety endpoints (ischemic cerebral or cardiac events) will be recorded every month via outpatient or phone review during follow-up.

Patients will use self-monitoring methods to monitor blood pressure during the follow-up. All patients are required to measure the blood pressure of the left brachial artery twice per week. Before blood pressure measurement, patients will be required to rest quietly for at least 5 min. Blood pressure will be measured using the YUYUE electronic sphygmomanometer (YE660A, China, which can record 40 data points in built-in memory). The data on blood pressure will be collected once a month (8-week blood pressure data will be collected from an electronic sphygmomanometer). The average of 8 systolic pressures will be calculated and used as the monthly pressure in statistical analysis.

For both randomized groups, protocol visit frequency will be monthly. During follow-up, outcome assessors who are blinded to patients’ treatment allocation will independently record all relevant events in detail:

UIA instability (the occurrence time, treatment and radiological data);Monthly self-monitoring blood pressure (8-week blood pressure data will be collected from an electronic sphygmomanometer. The average of 8 systolic pressures will be calculated and used as the monthly pressure);Ischemic cerebral or cardiac events (the occurrence time, treatment and radiological data).Regular follow-up head CTA [6 months (± 1 month) 12 (± 1 month) months, and 24 (± 1 month) months].

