### Statistical analysis

#### Sample size

The sample size is estimated using the PASS 15 (PASS Corporation, United States). In our preliminary studies, the 2-year instability events risk was approximately 20.7% in UIA patients with hypertension and 11.5% in UIA patients with controlled hypertension (17). In this study, we assume that EBPL could decrease the risk of aneurysm rupture and growth by 50%. At *α* = 0.05, *β* = 0.90, we need to enroll 506 patients (253patients in the SBPL group and 253 patients in EBPL group). By estimating the clinical dropout rate at 10%, the required sample size was calculated to be 282 patients in each group. This study prepared to include 570 patients in both groups (285 in each group), which could meet the statistical requirements.

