#### Endpoint and outcome evaluation

Before locking the database for analysis, we intend to test its plausibility and effectiveness. We will exclude the cases that could influence the accuracy of the conclusion. Patients who do not meet the requirement of quality control may be further excluded based on the consensus of the investigators’ discussion.

Categorical variables are presented as numbers (no.) and percentages (%). Continuous variables with normal distribution are expressed as means and standard deviation, and medians and inter-quartile range (IQR) if otherwise. The differences between groups in continuous variables are compared by performing the student’s t-tests or Wilcoxon rank sum tests, and the differences in categorical variables are compared using the chi-square tests or Fisher’s exact tests. The incident rate (IR) of PR and its 95% confidence interval (CI) are calculated. The univariate and multivariate Cox regression analyses are performed in PR-related analysis. The result of Cox regression analysis is presented as hazard ratio (HR) and 95% CI. SPSS 24.0 (SPSS, Chicago, IL) is used for statistical analysis, and bilateral *p* < 0.05 is considered statistically significant.

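### Angina is the only diagnosis in the primary safety composite that need not be new or worse than at baseline, so unchanged stable angina can count as an event and dilute the safety comparison

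*Protocol article*

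**What the plan says.** All references are to the protocol article.

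- **Outcomes and relative definitions, scope.** "The primary safety outcome is any ischemic cerebral or cardiac events during 24-month follow-up".
- **Same section, components.** "new or more frequent transient ischemic attacks, new clinical or radiological ischemic stroke, angina, new myocardial infarction, or reperfusion therapy for myocardial infarction".
- **Same section, definition of angina.** "Angina is defined as a transient chest pain or pressure (duration of symptoms < 30 min) caused by insufficient blood flow to the myocardium". The sentence goes on to require no significant ST/T change and no biomarker rise. It says nothing about onset, frequency or severity relative to baseline.
- **Exclusion criteria, named conditions.** "Patients with myocardial infarction, ischemic stroke, symptomatic heart failure during the past 3 months". Angina is not on this list.
- **Exclusion criteria, general clause.** "Any concurrent serious illness that would interfere with the outcome assessments including hepatic, renal, gastroenterological, respiratory, cardiovascular", followed by further organ systems.
- **Step 3: Outcome evaluation.** Aneurysm symptoms and safety endpoints "will be recorded every month via outpatient or phone review during follow-up".
- **Safety monitoring.** An Event Adjudication Committee has the final say on safety outcomes.

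**The concern.** The word *new* is repeated before myocardial infarction, directly after angina, so it cannot be read as carrying over from stroke to angina. Read literally, a patient who had stable effort angina before randomisation and has one more ordinary episode afterwards meets the outcome.

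The protocol avoids this problem elsewhere. TIA, the other transient ischemic symptom in the composite, is tied to the patient's previous pattern. In the efficacy outcome, sentinel headache and seizure are both conditioned on the absence of a relevant history. Angina is the exception.

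The Discussion frames the trial as asking whether the lower target prevents instability with no rise in ischemic events. Events that reflect disease present at entry say nothing about the blood pressure target. They enter both arms alike and make the arms look more similar in relative terms, which is the reassuring direction on a safety question.

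**Working it through.** **1. The text, component by component**

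| Component | Baseline condition in the composite | Added by its definition |
|---|---|---|
| TIA | new or more frequent | not needed |
| Ischemic stroke | new | not needed |
| Angina | none | none |
| Myocardial infarction | new | not needed |
| Reperfusion therapy for infarction | none | not separately defined; a procedure, not a diagnosis |

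Angina is the only diagnosis without a condition.

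**2. The plan's own figure**

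The plan states no event rate, margin or power for the safety composite, so there is no safety figure to reproduce. Its only calculation is for efficacy: "At *α* = 0.05, *β* = 0.90" (the 0.90 read as power), two-sided as in "bilateral *p* < 0.05 is considered statistically significant", with 20.7% halved to 10.35%. With unpooled variance:

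n = (1.960 + 1.282)² × (0.207×0.793 + 0.1035×0.8965) / 0.1035² = 252.03, rounded up to 253 per arm. Then 253/0.90 = 281.1, rounded up to 282.

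Both match the Sample size section. The 253 evaluable patients per arm are used below.

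**3. Effect of counting prevalent angina**

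Assumed inputs, none of them in the document:
- incident 24-month risk r of 3% (standard arm) and 6% (enhanced arm), a true ratio of 2.0;
- a share q of patients, equal in both arms, who have angina at entry and score on an unchanged episode;
- the same incident risk whether or not the patient has angina at entry.

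Formulas:
- observed risk = q + (1 − q) × r
- risk difference = (1 − q) × (true difference)
- power = Φ{ [d√n − 1.96√(2p̄(1 − p̄))] / √(p₀(1 − p₀) + p₁(1 − p₁)) }, where n = 253, d = p₁ − p₀ and p̄ is the mean of the two risks.

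Worked at q = 5%: 0.05 + 0.95×0.03 = 0.0785 and 0.05 + 0.95×0.06 = 0.1070, so the ratio is 1.36.

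Worked at q = 8%: 0.08 + 0.92×0.03 = 0.1076 and 0.08 + 0.92×0.06 = 0.1352, so the ratio is 1.26. Power: (0.0276×√253 − 1.96×√(2×0.1214×0.8786)) / √(0.1076×0.8924 + 0.1352×0.8648) = (0.439 − 0.905)/0.461 = −1.01, which gives about 16%.

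| q | Standard | Enhanced | Ratio | Difference (points) | Power |
|---|---|---|---|---|---|
| 0% | 3.0% | 6.0% | 2.00 | 3.00 | 37% |
| 2% | 4.9% | 7.9% | 1.60 | 2.94 | 27% |
| 5% | 7.9% | 10.7% | 1.36 | 2.85 | 20% |
| 8% | 10.8% | 13.5% | 1.26 | 2.76 | 16% |
| 10% | 12.7% | 15.4% | 1.21 | 2.70 | 14% |

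With assumed incident risks of 5% and 10% instead:

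| q | Standard | Enhanced | Ratio | Power |
|---|---|---|---|---|
| 0% | 5.0% | 10.0% | 2.00 | 57% |
| 2% | 6.9% | 11.8% | 1.71 | 47% |
| 5% | 9.8% | 14.5% | 1.49 | 37% |
| 10% | 14.5% | 19.0% | 1.31 | 27% |

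**4. Reading q**

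q equals the prevalence of angina at entry only if every prevalent case scores. If half of them do, a 4% prevalence gives the 2% row. Reading the tables by prevalence therefore gives an upper bound.

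**The case against.** Much of the case on the other side is sound.

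- **Eligibility.** If prevalent angina contaminates the safety outcome, the general clause on serious illness that interferes with outcome assessment arguably covers it. This stands in part. Some patients will be kept out, but the clause requires serious illness and leaves the judgement to the site, so mild stable angina is not clearly excluded.
- **Scoring is not automatic.** A reader might infer that every patient with stable angina becomes an event at the first monthly contact. The document does not support that. The definition presupposes an ECG and a biomarker test, which a telephone report does not supply, and events are assessed by blinded investigators and finally by a committee. This limits how many cases score. It does not remove the problem, because blinded assessors who apply the written definition correctly would still count a documented, unchanged episode.
- **Later events lost to a Cox model.** A reader might also infer that early angina displaces later strokes or infarctions in a time-to-first-event analysis. Cox models are stated for the safety endpoint only in the subgroup plan, and all ischemic events are to be recorded with their timing, so component counts remain available. The point does not rest on this.
- **Low power anyway.** At 3% against 6%, power is only 37% with no prevalent angina at all. The wording is therefore not the main reason a harm could be missed, though it makes a weak comparison weaker.
- **Baseline data.** Table 1 lists baseline clinical information, and the article need not itemise the case report form. Angina history may already be collected.

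**Conclusion.** The inconsistency is real and lies in a stated rule, not in omitted detail. As written, an unchanged habitual episode of angina can count as a primary safety event, and nothing in the eligibility criteria clearly prevents it.

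The supported consequence is that such events can dilute the ratio and reduce power. It would go too far to say that the wording masks ischemic harm. The absolute excess is nearly preserved, falling from 3.00 to 2.76 points even at 8%, and neither the prevalence nor the event rate is given.

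The fall in the ratio from 2.0 to between 1.60 and 1.26 rests on four assumptions: incident risks of 3% and 6%, a prevalence of 2% to 8%, full conversion of prevalent cases to events, and balance between arms. Conversion below 100% makes the effect smaller. The direction, toward no difference, holds as long as the arms are balanced.

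**What to change.** In Outcomes and relative definitions, replace the bare term in the composite with *new-onset angina, or angina more frequent or more severe than at baseline*, parallel to the TIA wording. Put the same condition in the definition of angina. Confirm that angina history and usual frequency are recorded with the baseline clinical information, and have the Event Adjudication Committee judge reported angina against that record while blinded to allocation.

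The cost is a few words and, if not already present, one baseline item on the case report form. The downside is slightly fewer safety events; those removed reflect angina already present and unchanged since entry.

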### Quality control of the research

To avoid bias and ensure patients’ medical adherence, we follow the standards in the subsequent text:

Self-monitoring of blood pressure: According to the recommendation of China’s guideline for hypertension (2018) (16), we will use the home blood pressure monitoring method to monitor patients’ blood pressure monthly. All patients will receive training for blood pressure measurements from professional cardiologists at enrollment and every 3 months. We will evaluate pre-enrollment medication adherence and include only patients with good adherence. We will require all patients to measure the blood pressure of the left brachial artery twice at least 1 min apart in the morning before breakfast and taking antihypertensive medications, and after urination and defecation. Before blood pressure measurement, all patients will be required to rest for at least 5 min. Blood pressure is measured using the YUYUE electronic sphygmomanometer (YE660A, China). Researchers will collect blood pressure data once a month.Protocol-noncompliance: If the patient’s SBP does not reach the assigned target during follow-up, the cardiologists will evaluate the patient according to the predefined antihypertensive treatment algorithm (Figures 2, 3).Unable to complete the required CTA examinations: We will contact each patient one month before the CTA examination by telephone to ensure completion. If patients are unable to complete CTA examinations in the required time interval, they will not be included in the final analysis.

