### Safety monitoring

Each participating investigator has primary responsibility for the safety of the individual participants under his/her care. At each follow-up, CRC will specifically query participants for adverse events (AE) and serious adverse event (SAE) and recorded them in the case report form (CRF). Event Adjudication Committee members are responsible to make final ascertain of safety outcomes.

In our current study, adverse event (AE) is defined as any intervention related unfavorable medical outcomes, including any clinically obvious symptom, abnormal sign, or disease. In our current study, we will monitor AE including hypotension, dizziness, angioedema, headache.

Adverse event is considered as serious adverse event (SAE) only when it met following criteria: fatal or life-threatening, result in significant or persistent disability, or require hospitalization or surgical intervention, including:

Symptomatic hypotension.Arrhythmia.Acute kidney failure.Electrolyte abnormalities.Injurious falls.Syncope.Unexpected events for which the investigator believes that intervention caused the event or contributed to the immediate cause of the event.

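### Fatal MI or stroke can count in the safety composite, but the CTA exclusion, a conflicting stroke definition and the absence of any death outcome handle fatal ischemic events badly

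*Protocol article*

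**What the plan says.** All references are to the protocol article.

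- **Outcomes and relative definitions, component list.** The primary safety outcome is any ischemic cerebral or cardiac event over 24 months. It includes new or more frequent TIA and "new clinical or radiological ischemic stroke, angina, new myocardial infarction, or reperfusion therapy for myocardial infarction". The secondary outcomes are rupture, growth and change in wall enhancement. Death is not listed in any form.
- **Same section, stroke.** The list admits "new clinical or radiological ischemic stroke". The definition that follows describes a persistent deficit "which shows acute hypodense infarction area on NCCT images and T2-weighted MRI".
- **Same section, MI.** MI is "myocardial necrosis in clinical settings consistent with myocardial ischemia". The text then says "These conditions can be satisfied by a rise of cardiac biomarkers" together with at least one of five further findings, one of which is thrombus at angiography or autopsy.
- **Step 3: Outcome evaluation.** The "safety endpoints (ischemic cerebral or cardiac events) will be recorded every month via outpatient or phone review during follow-up".
- **Quality control of the research.** "If patients are unable to complete CTA examinations in the required time interval, they will not be included in the final analysis".
- **Safety monitoring.** An "adverse event (AE) is defined as any intervention related unfavorable medical outcomes". Fatality appears here only as a criterion of seriousness. The open-ended SAE item is confined to events that the investigator attributes at least partly to the intervention. An Event Adjudication Committee makes the final decision on safety outcomes.

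**The concern.** The Discussion frames the question as whether enhanced lowering can prevent instability without raising ischemic risk. That conclusion needs the worst ischemic events to enter the comparison at least as reliably as the mild ones. As written, a chest pain of under 30 minutes without ECG or biomarker change counts as angina. A patient who dies of an ischemic event may be removed by the CTA rule, fail the stroke definition for want of imaging, or depend on an unwritten committee decision. The CTA rule matters most, because it excludes patients as a consequence of the outcome itself.

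**Working it through.** The article gives no event rate for the safety composite and no mortality rate, so there is no plan figure to reproduce. The first three steps compare the rules; the fourth is an illustration under assumed rates.

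**1. CTA exclusion.** CTAs are due at 6, 12 and 24 months, each ± 1 month. Take a troponin-confirmed fatal MI at month 10. It meets the MI definition and is picked up at the monthly review. The 12-month window opens at month 11, so the 12- and 24-month CTAs cannot be done and the patient is left out of the final analysis. More generally, any death before month 23 misses at least the last CTA. The rule has no exception for death and none for the safety analysis.

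**2. Stroke.** A persistent deficit with no imaging satisfies the list (a clinical stroke) and fails the definition (infarction on CT and T2-weighted MRI). It is not a TIA either, since a TIA must resolve within 24 hours. This affects any unimaged stroke, fatal or not.

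**3. Sudden cardiac death before testing.** The only MI route spelled out starts with a biomarker rise; autopsy thrombus is an addition to that rise, not a substitute. No rule covers death without a sample. AE and SAE reporting does not fill the gap, because it is limited to events judged related to the intervention and is not a listed outcome.

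**4. Size (assumed rates).** Inputs: 285 per arm (Sample size section). Assumptions: 2-year all-cause mortality 0.5% to 2%, with 10% to 50% of deaths from an ischemic cerebral or cardiac cause.

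- Low: 285 × 0.005 × 0.10 = 0.14 fatal ischemic events per arm.
- High: 285 × 0.02 × 0.50 = 2.85 per arm.
- One event is 1/285 = 0.35 percentage points.

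Suppose both arms truly have 14 events: 14/285 = 4.91%, RR 1.00, SE(log RR) = √(2/14 − 2/285) = 0.369, 95% CI exp(±1.96 × 0.369) = 0.49 to 2.06. Let the CTA rule remove k patients with fatal events from one arm only, from numerator and denominator:

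| k | Rate in affected arm | RR if lost under EBPL | RR if lost under SBPL |
|---|---|---|---|
| 1 | 13/284 = 4.58% | 0.93 | 1.07 |
| 2 | 12/283 = 4.24% | 0.86 | 1.16 |
| 3 | 11/282 = 3.90% | 0.79 | 1.26 |

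Equal losses in both arms leave the RR at 1.00. These shifts describe the CTA exclusion. They do not measure the missing death component alone, under which fatal events that meet the MI or stroke definition would still be counted and fewer would be lost.

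**The case against.** A reader might infer from the component list that fatal events are left out of the safety outcome. The document does not support that. The umbrella wording covers any ischemic cerebral or cardiac event, MI and stroke are not restricted to survivors, and the mention of autopsy shows that deaths were contemplated. Nor is a sudden cardiac death clearly shut out: the biomarker route is given as one way to satisfy the MI definition, a sufficient condition and not a necessary one. The committee has the final say, and its handling of sudden death could sit in a charter or full protocol that is not shown.

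The open-label design should not be overplayed either. Two investigators unaware of patient information assess ischemic events, and assessors blinded to allocation record them. The relatedness filter acts on AE and SAE reporting, not on the primary safety outcome. Eligibility also removes patients with recent MI, stroke or heart failure and those expected to survive less than 2 years, which makes the upper end of the assumed range less likely.

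It is fair, too, that the CTA rule is a general analysis-population problem and was plausibly written with non-attenders in mind, since it follows a telephone reminder. The stroke conflict likewise is not specific to fatal events.

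All of this narrows the point but leaves its core. Neither blinded assessment nor adjudication returns a patient whom the CTA rule has excluded. The stroke conflict is on the face of the text. Discretion without a stated rule is a weak basis for classifying the most serious events.

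**Conclusion.** The point stands in limited form. Fatal MI and stroke meeting the definitions count, but the CTA rule read literally then removes the patient, the stroke list and definition disagree, and untested sudden cardiac death has no stated rule and no mortality outcome behind it.

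The numerical effect is probably small: about 0 to 3 fatal ischemic events per arm, all inputs assumed. Even three one-sided losses move the RR only to 0.79 or 1.26, well inside a 95% CI of 0.49 to 2.06. A reader might conclude that the safety comparison is biased towards enhanced lowering. That does not follow. The Discussion says intensive lowering may increase ischemic events, while the Introduction cites a trial in which a target below 120 mmHg reduced major cardiovascular events, so the direction is unknown. The case for change rests on rules that mishandle the gravest events, not on a demonstrated bias.

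**What to change.** 1. Quality control section: exempt patients who die from the missing-CTA exclusion, and analyse the safety outcome in all randomised patients.
2. Stroke definition: bring it into line with the clinical or radiological wording of the component list.
3. Safety composite: add death adjudicated, blinded to arm, as due to an ischemic cerebral or cardiac cause, with no biomarker or imaging requirement for fatal events.
4. Report all-cause death by arm in all randomised patients, whatever the judged relatedness.
5. Have the existing committee classify sudden deaths of unknown cause separately and include them only in a sensitivity analysis. Some may be aneurysm ruptures, which belong to the efficacy endpoint and would distort the safety comparison.

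The cost is an outcome-definition amendment and one CRF line for date and cause of death, using the monthly contacts and the committee already in place. The downside is a little extra adjudication and some misclassification of cause of death.

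### The ischemic-event definitions are narrower than the primary safety composite and leave some events in no category; separately, the adverse-event definition depends on attribution

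*Protocol article*

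**What the plan says.** All references are to the protocol article.

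**Composite (Outcomes and relative definitions).** The primary safety outcome is any ischemic cerebral or cardiac event over 24 months. Its listed components are new or more frequent TIA, then "new clinical or radiological ischemic stroke, angina, new myocardial infarction, or reperfusion therapy for myocardial infarction". The article then introduces definitions for these events.

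**Definitions (same section).**
- Stroke: a deficit that persists, of ischemic origin in the brain, cord or retina. The imaging limb is worded "which shows acute hypodense infarction area on NCCT images and T2-weighted MRI".
- TIA: "TIA is defined as a transient episode (duration of symptoms < 24 h) of neurological dysfunctions", with no acute infarct on non-contrast CT (NCCT).
- Angina: chest pain or pressure of less than 30 minutes, "caused by insufficient blood flow to the myocardium without significant ST/T changes in ECG and rise of cardiac biomarkers".
- Myocardial infarction: a biomarker rise plus at least one further criterion.

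**Adverse events (Safety monitoring).** An "adverse event (AE) is defined as any intervention related unfavorable medical outcomes". An adverse event becomes serious only if it meets the seriousness criteria, so serious events are a subset of adverse events. The section names events to watch for. Among the serious ones, only the last item (unexpected events) carries its own condition about the investigator's belief in causation.

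**Capture (Step 3: Outcome evaluation; Safety monitoring).** Ischemic events are recorded monthly with no relatedness condition. Outcome assessors are blinded, and an Event Adjudication Committee makes the final determination of safety outcomes.

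**The concern.** The composite and the definitions meant to implement it do not agree. The composite accepts a stroke on clinical or on radiological grounds. The definition asks for the clinical and the imaging finding together, and words the imaging limb as NCCT and T2-weighted MRI. The TIA, angina and infarction definitions do not pick up everything that the narrower wording leaves out.

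This matters because the Discussion makes safety half of the trial's question: whether enhanced lowering prevents instability without more ischemic events, while acknowledging that intensive lowering may raise that risk. A finding of no increase is only as informative as the number of events behind it. Two committees working from this text could also return different counts for the same patients.

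The adverse-event wording raises a different problem. When relatedness is part of the definition and treatment is open-label, the count can reflect what staff expect of each target as well as what happened.

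**Working it through.** **1. Setting the definitions side by side.** Each event below is tested against every category.

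| Event | TIA | Stroke | Angina | MI |
|---|---|---|---|---|
| Deficit ≥ 24 h, NCCT negative (with or without an MRI infarct) | no: duration | no: NCCT limb | – | – |
| Silent infarct on imaging | no: no symptoms | no: no deficit | – | – |
| Ischemic chest pain ≥ 30 min, no biomarker rise | – | – | no: duration | no: biomarker |
| Deficit < 24 h with infarct on NCCT | no: infarct | depends on the meaning of persistent | – | – |
| Pain < 30 min with ST/T change, no biomarker rise | – | – | depends on the reading | no: biomarker |

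The first three rows are gaps on the plain wording. Persistent retinal or spinal-cord ischemia without an NCCT hypodensity is a special case of row 1: the stroke definition names it and its imaging limb then excludes it. The composite's own words would admit row 1 as a clinical stroke and row 2 as a radiological one, which is the contradiction.

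The last two rows depend on interpretation. No hour threshold is attached to the persistent deficit, so excluding row 4 is an inference from the TIA limit. In row 5, if the angina exclusion means neither ST/T change nor biomarker rise, the event fits nowhere. If it means not both together, row 5 is angina, but brief pain with a biomarker rise and no ST/T change then meets both angina and MI. Either reading needs repair.

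**2. Size.** The article states no safety event rate, margin or safety power, so there is no figure of the plan's to reproduce. What follows is illustration.

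Inputs: 285 per arm (Sample size); assumed 24-month risk of 3% per arm, with 5% as a second value; hazard ratio 1.0; the same fraction of events lost in both arms.

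Upper 95% limit = exp(1.96 × √(2/e)), where e is the number of events counted per arm.

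| Events lost | e at 3% | Upper limit | e at 5% | Upper limit |
|---|---|---|---|---|
| 0% | 285 × 0.03 = 8.55 | 2.58 | 285 × 0.05 = 14.25 | 2.08 |
| 20% | 6.84 | 2.89 | 11.40 | 2.27 |
| 30% | 5.99 | 3.11 | 9.98 | 2.41 |
| 50% | 4.28 | 3.82 | 7.13 | 2.82 |

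At 3%, the reported risk falls to 2.4%, 2.1% or 1.5%. With the plan's 10% dropout, e with no loss is 8.55 × 0.9 = 7.70 and the starting limit is 2.72.

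**3. If harm exists.** Assume true risks of 3% and 6%, 285 per arm and a two-sided 5% test. Power = Φ{[|p₁−p₂|√n − 1.96√(2p̄(1−p̄))] / √(p₁(1−p₁)+p₂(1−p₂))}, with each risk multiplied by the captured fraction.

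| Captured | Risk difference (points) | Risk ratio | Power |
|---|---|---|---|
| 100% | 3.0 | 2.0 | 0.41 |
| 80% | 2.4 | 2.0 | 0.34 |
| 60% | 1.8 | 2.0 | 0.26 |
| 50% | 1.5 | 2.0 | 0.23 |

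Equal loss shrinks the difference and the power. The ratio does not move.

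**4. Adverse events.** The general definition requires relatedness, and serious events inherit it. Yet syncope, acute kidney failure and injurious falls are listed as serious events with no causality condition of their own. Under the general definition an unrelated fall is not an adverse event; under the list it may be. The section does not say which governs.

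**The case against.** The best defense has three parts.

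First, the outcome is introduced as any ischemic cerebral or cardiac event. Blinded assessors and an adjudication committee could apply that wording, in which case clinical strokes without the imaging finding and silent infarcts both count. The committee's charter is not shown. This stands as a reason not to say that events will be lost. It does not remove the defect: blinding and adjudication do not settle which of two conflicting texts applies, and the composite's wording does not place chest pain of 30 minutes or more without a biomarker rise.

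Second, a reader might infer that harm from enhanced lowering in particular is being hidden. The documents do not support that. The same definitions apply to both arms under blinded assessment, so the expected effect is loss in both.

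Third, a reader might infer that adverse events are recorded only after an unblinded investigator rules them treatment-related. No such step is described: the research coordinator asks about events at each follow-up and records them, and several named events have no causality condition. Attribution in an open-label trial could also raise the enhanced arm's count, so no direction follows. Nor does the restriction reach the primary safety outcome, which Step 3 records without regard to cause. What remains is an unclear definition through which attribution can enter the counts.

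**Conclusion.** The point holds in this form. The ischemic-event definitions contradict the composite on stroke and are not exhaustive: three kinds of event fit no category on the plain wording, and two more may not, depending on how the text is read. The primary safety outcome may therefore be undercounted in both arms, with lower counts, a smaller risk difference and less precision, but no bias in the ratio from this alone.

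The size cannot be taken from the document. The illustrated rise in the upper limit rests on an assumed risk of 3%, a hazard ratio of 1.0, equal loss of 20% to 50%, and 285 analyzed per arm; a higher risk gives narrower limits throughout.

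The adverse-event definition is a separate and lesser defect that affects only the adverse and serious adverse event tables. It should be corrected, since both repairs are textual.

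**What to change.** - Reconcile the event definitions with the composite, so that a stroke qualifies on clinical or on radiological grounds and every ischemic cerebral or cardiac event falls in exactly one category. Base the classification on whatever imaging was done, not on a required pair of scans.
- State how a short deficit with an infarct is classed, and reword the angina exclusion so that it has one meaning and meets the MI definition without gap or overlap.
- Define an adverse event as any untoward event after randomization regardless of cause, and a serious one by seriousness alone. Put relatedness in a separate case report form field, and compare all serious events and deaths by arm.

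The cost is definition text and one form field, with no additional scheduled tests. The small downside is more events to record and adjudicate. Events already classified under the present wording should be re-read against the reconciled definitions without knowledge of allocation.
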